**2. Project aims**

**a.** The overall objective is to investigate the feasibility and acceptability of the theory-based and internationally tested intervention, Youth-Physical Activity Towards Health (Y-PATH), within a Danish school context, informed by the Medical Research Council (MRC) framework and The Common Guidelines for Education Research and Development. The goal is that a revised and adapted and feasible intervention protocol, that aims to increase pupils’ PL, will be ready for effectiveness testing by the end of this project.

The project will contribute to the PL research field by providing a revised PL intervention, a Template for Intervention Description and Replication (TIDieR) checklist, intervention materials, and a protocol that offers a solid empirical and theoretical foundation for a future upscaled effectiveness study to be developed and implemented.

The investigation will be guided by the following research question: is the Y-PATH intervention feasible and acceptable in a Danish school context among pupils in 4^th^ and 5^th^ grade (9-11 years of age)?

**b.** The burden of non-communicable diseases (NCDs) is a rising problem, and the increase in physical inactivity across the world is costly to societies (1). However, the focus on the importance of physical activity (PA) is considerable, yet maintaining sufficient levels of PA is becoming more and more difficult (2,3). Internationally, three in four adolescents, do not currently meet the global recommendations set by the World Health Organization (WHO) (4). Further, a considerable number of Danish children and adolescents do not meet the national physical activity (PA) recommendations (5). It is well-documented that regular PA and decreased sedentary time contribute to the prevention of NCDs as well as NCD risk factors such as e.g. overweight and obesity (4). Despite the well-known benefits of regular PA – promoting mental and physical health across the lifespan – and the evidence that early health behaviors track into adolescence and adulthood (6), studies suggest that PA participation decline notably during adolescence (5,7), with girls being significantly less active than boys (5,8).

The school is considered a key setting to promote PA among children and adolescents. Yet only a few school-based interventions aiming to increase PA, identified small effects, and none, to our knowledge, has shown long-term effects (9,10). Multicomponent interventions that combine two or more intervention approaches such as curricular and non-curricular areas, e.g. physical education lessons, school recess, and after-school leisure time, have shown to be a promising approach to increasing children and adolescents’ PA (11,12). In addition, studies suggest that school-based interventions aiming to increase PA should apply a theoretical basis involving the whole school community comprising e.g. teachers, school managers, and parents (13,14). Further, a crucial factor for the acceptability of a school-based intervention is that it aligns with the schools’ core business and is not a so-called “add-on” to the existing educational curriculum, but an intervention using an “add-in” approach contributing to the core goals of the educational curriculum (15). Besides the small effect sizes identified in school-based interventions aiming to increase PA, it has also been identified that PA is context dependent and thus cannot be treated as a trait.

The concept of physical literacy (PL) has gained popularity worldwide and is a comprehensive multidimensional concept that has been identified as a ‘cause of the causes’. PL consists of the dimensions that lay the foundation for an individual’s capacity and tendency to engage in PA throughout life. Few interventions, however, targeting PL exist on a global scale. In Denmark, the development of theoretically driven and evidence-based PL interventions that aim to increase children and adolescents’ PL are still in their infancy. Yet, a promising theory-based and internationally tested intervention, Youth-Physical Activity Towards Health (Y-PATH), has proven to be effective on children and adolescents’ PA levels, motor skills, and PL in Ireland.

The Y-PATH intervention is a multicomponent holistic school-based intervention based on the theory of PL as well as self-determination theory and the socioecological model (16, 17, 18). The intervention is organized with four core components targeting both pupils, teachers, and parents/guardians, and works through a PE component, a teacher component, a parent/guardian component, and a website component (Figure 1). Y-PATH is facilitated within the principles of ‘add in’ approach to school health promotion as the intervention supports delivery of existing national PE curriculum in schools and does not create additional workload for PE teachers.

The primary aim of Y-PATH is to improve the prerequisites for engagement in lifelong PA, through an improvement of the PL domains. That is, by 1) providing education (improving knowledge and understanding) about the importance of PA for health and the risk of sedentary behavior 2) increasing fundamental movement skills proficiency essential for PA participation, and 3) improving levels of self-efficacy, confidence, motivation, regulation, and empowerment related to PA.

**Figure 1**

The Y-PATH intervention components

**
[figure not shown]
**

**3. Methods**

**a.** The study builds on a cluster randomized controlled trial (RCT) pilot study and will be carried out in four Danish schools in two different municipalities. The four participating schools will be randomly assigned to either intervention or control conditions using a simple randomization method by drawing a lot. We randomly choose one intervention school and one control school in each municipality. The randomization is done at the school level because the intervention will be facilitated to an entire school – such randomization minimizes the likelihood of unwanted influences on teachers in the control condition, e.g., gaining inspiration from the intervention condition. The school randomized to the intervention condition will receive the intervention, while the control school will be requested to carry out traditional curriculum-based physical education teaching. The control school will, however, be offered the opportunity to receive the intervention the following academic school year. Eligible classes for the study involve 4^th^ and 5^th^ graders, i.e., classes with pupils being 9-11 years of age. Given an approximated mean of 21 pupils per class and two classes per grade, a minimum of 168 pupils will be recruited to receive the intervention.

**b.** Feasibility and acceptability of the intervention will be consistent with guidance proposed by the Medical Research Council (MRC) and The Common Guidelines for Education Research and Development. The evaluation will use a mixed-method approach to assess the primary outcomes – feasibility and acceptability of the Y-PATH intervention. While the quantitative measures will provide knowledge of the intervention effects on pupils’ PL, the qualitative evaluation will provide insights as to why the intervention was effective or not in a Danish school setting. This contributes to potential cultural, context, and age-related alterations. The procedure description is divided in the following: teacher workshop/course, effectiveness, acceptability, and demand experiences, and parents’ questionnaire. An overview of the data collection process can be found in Figure 2. Further, a detailed protocol for the adaptation process can be found online at <https://osf.io/wd5ur/>.

Teacher course: in this study, the intervention teachers will receive a 4-hour face-to-face course and an additional 1,5-hour online course (four modules of 15 to 20 min.) about PL, motivation, and well-being. The PE teachers will receive six detailed PL-based lesson plans which should be delivered in their PE classes. After following the six lesson plans, the teachers will prepare and deliver PL focused PE classes for the rest of the school year. The teachers will be provided with online resources and inspiration materials

Test of effectiveness*:* a design for testing intervention effect will also be tested. This will include administering physical tests and questionnaires. The preliminary effectiveness will be tested by comparing changes in pupils’ PL over time. PL will be assessed with a CAMSA test, pacer test, plank test, and a video-assisted version of the Danish myPL questionnaire and the validated Danish Assessment of Physical Literacy (DAPL) tool, i.e., that was developed in our ongoing project CAPL-2D supported by the TrygFonden (#125640). Furthermore, the children will wear an activity tracker (an accelerometer) for one week twice, i.e., before and after the intervention. Axivity® AX3 accelerometers (23 x 32.5 x 7.6 mm, please see Figure 2) will be mounted with skin tape (with the following brands: Fixomull tape (BSN Medical), adhesive hair-set tape by the investigator to each of the pupils’ left thigh. The effect on pupils’ well-being will also be assessed. This will be assessed using a video-assisted version of KIDSCREEN-27 for 9-11-years-old children as well as a parent-reported version the Strength and Difficulties Questionnaire (SDQ).

Acceptability and demand experiences: the acceptability, including demand and experiences, and the intervention implementation degree, will be evaluated using short bimonthly questionnaires to teachers as well as three observations during the intervention period i.e., one schoolyear. As for the monitoring of the acceptability of the interventions’ materials and resources, the PE teachers will receive a short questionnaire after their weekly PE class – one targeted the six given lesson plans and another one targeted the remaining PE classes. The questions will be related to their PE lessons and their experiences with the focus on PL. As for the three observations, the validated observation tool ‘Multidimensional Motivational Climate Observation System’ will be used in a slightly context-adapted version. Also, the involvement of PL within the PE classes will be observed. The feasibility of the practicality and the recruitment process as well as the costs related to the activities in the project will be assessed within a document log administered by trained research assistants.

Furthermore, interviews will be conducted with pupils, teachers, parents, and school managers after the end of the intervention. Interviews will also be conducted with teachers after the delivery of the six preplanned lesson plans.

Parents’ questionnaires: parents will receive a survey on background information before the start of the intervention as well as an evaluation survey after the intervention.

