**5. Participants**

**a.** Eligible classes for the study involve 4^th^ and 5^th^ graders, i.e., classes with pupils being 9-11 years of age.

A total of four public schools with a minimum of two classes per grade will be recruited and randomized to either the intervention or control condition.

The inclusion criteria are the following:

School/class-level

- Non-special needs municipal school classes
- Classes that are not in other school development or research projects which would most likely influence and bias the results

Pupil-level

- Pupils with parents/guardians who have provided written informed consent, allowing their child to participate

Pupils who have provide an oral assessment

**b.** None in addition to the inclusion criteria provide above.

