**12. Recruitment of participants and informed consent**

**a.** The recruitment will proceed through school managers and teachers who will be contacted via e-mail, receiving a recruitment letter and information flyers about the project and participation. Prior to the data collection, parents/guardians of pupils invited to participate in 3PL project will fill out a written informed consent.

**c.** Parents/guardians of pupils invited to participate in the project, will be requested to complete a written consent before data collection. By signing they confirm that they give their child permission to participate. If parents have provided a written consent allowing their child to participate, the child will receive age-appropriate oral information about the project and further be asked to provide an oral assessment. Only when both written consent and oral assessment is obtained, the data will be collected on the respective child.

All data will be stored electronically on a secure drive. The drive will be created by the Center for IT Medico and Technology (CIMT) via a network-file server, as a so-called ‘closed-drive’, which will be logged i.e., CIMT logs who have access to the drive. The drive will be created in accordance with current practice for securely storing personal and sensitive data.

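### The stated minimum of 168 recruited pupils is the expected class roll of the intervention schools at full consent, so it is not assured as a minimum

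*Protocol*

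**What the plan says.** Section 3a (Methods) gives the protocol's only pupil number: "a minimum of 168 pupils will be recruited to receive the intervention". It derives the number in the same sentence: "Given an approximated mean of 21 pupils per class and two classes per grade". The trial "will be carried out in four Danish schools in two different municipalities", with one school drawn for intervention and one for control in each municipality. Section 11 (Remuneration) confirms that there are two intervention schools. The eligible grades are the 4th and 5th.

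Section 5 (Participants) sets the entry requirement for schools: "A total of four public schools with a minimum of two classes per grade will be recruited". Two classes per grade is therefore the least a school may bring. At pupil level the same section includes "Pupils with parents/guardians who have provided written informed consent, allowing their child to participate", and it also lists the child's oral agreement. Section 12 repeats the double condition: "Only when both written consent and oral assessment is obtained, the data will be collected on the respective child".

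The protocol states no expected consent rate. Section 4 says that the analysis is mostly descriptive and that recruitment, attrition and questionnaire response will be summarised and compared between conditions.

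**The concern.** A minimum number recruited should hold in the least favourable case that the design admits. Here the number comes from multiplying an average class size by the number of classes, with no allowance for families who decline. At the entry requirement for schools, it is therefore the number reached when everyone agrees. An average class size is not a lower bound either.

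This matters because feasibility is a primary outcome of the pilot, and the recruitment process is one of the things it sets out to assess. A planned figure equal to full uptake is no realistic benchmark for the observed recruitment. It also leaves unclear which of two groups is being counted: the pupils who sit in classes where the intervention is taught, or the pupils who are enrolled and may be measured. The uptake rate that a later trial needs is the ratio of the second group to the first, so the plan should keep them apart.

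**Working it through.** **Inputs**

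- Pupils per class: 21, an approximate mean (section 3a).
- Classes per grade: 2 in the calculation (section 3a); at least 2 as the entry requirement (section 5).
- Grades: 2 (sections 3a and 5).
- Schools: 4, of which 2 are intervention schools (sections 3a and 11).
- Consent rate: none stated. The rates below are assumptions chosen to show a range.

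**Step 1. Reproduce the plan's figure**

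Roll = pupils per class × classes per grade × grades × schools.

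- One school: 21 × 2 × 2 × 1 = 84
- Two schools: 21 × 2 × 2 × 2 = 168
- Four schools: 21 × 2 × 2 × 4 = 336

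Only two schools give 168. The figure is the full expected roll of the intervention arm (8 classes of 21), with consent implicitly at 100%. The same inputs imply 168 in the control arm and 336 in all.

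**Step 2. Apply the consent condition at two classes per grade**

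Consented pupils = roll × consent rate.

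| Assumed consent | Intervention arm (168 × rate) | Both arms (336 × rate) |
|---|---|---|
| 100% | 168 | 336 |
| 95% | 159.6, about 160 | 319.2, about 319 |
| 90% | 151.2, about 151 | 302.4, about 302 |
| 80% | 134.4, about 134 | 268.8, about 269 |
| 70% | 117.6, about 118 | 235.2, about 235 |

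**Step 3. Roll needed for 168 consented intervention pupils**

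Roll needed = 168 / consent rate; classes needed = roll / 21, rounded up.

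- 90%: 168 / 0.90 = 186.7, so 187 pupils, or 9 classes
- 80%: 168 / 0.80 = 210 pupils, or 10 classes
- 70%: 168 / 0.70 = 240 pupils, or 12 classes

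The plan's calculation uses 8 classes. With 8 classes, the mean class size would have to be 21 / rate: 23.3, 26.2 and 30.0 respectively.

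**Step 4. Can the design still reach 168?**

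Section 5 allows more than two classes per grade.

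- One intervention school with three per grade: 21 × (4 + 6) = 210 pupils; 168 / 210 = 80% consent is enough.
- Both with three per grade: 21 × 3 × 2 × 2 = 252 pupils; 168 / 252 = 66.7% consent is enough.

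So 168 is attainable under the design, but not guaranteed by it.

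**The case against.** The strongest defence has two parts.

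First, two classes per grade is itself a floor, and the word minimum in section 3a may simply carry that floor forward. This stands in part. A reader might infer that the design cannot deliver 168. Section 5 does not support that, since larger schools reach 168 with 80% or 66.7% consent (step 4). However, this rescue relies on schools above the entry requirement, whereas section 3a calculates the case of exactly two classes per grade.

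Second, the sentence concerns pupils who receive the intervention. The intervention goes to whole schools through ordinary PE lessons, recruitment runs through school managers and teachers, and the rule in section 12 governs data collection. On that reading a class headcount is the natural number, and 168 is a fair expected number exposed. This also stands in part. But the sentence speaks of recruited pupils, section 5 makes parental consent a pupil-level inclusion criterion, and even as an exposure count the figure is an average and not a lower bound.

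Three further inferences may tempt a reader and should not be drawn:

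- That later drop-out makes the shortfall larger. Section 3a makes no claim about pupils retained or measured after the intervention, so attrition does not bear on a recruitment figure.
- That the figure distorts the precision of the pilot's rates. The protocol bases no interval, power calculation or progression threshold on 168, and observed rates will rest on observed counts.
- That the absence of a control or total number is an error. It is missing detail only, since 168 and 336 follow directly from the stated inputs.

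**Conclusion.** The point holds as a misstatement of what 168 represents. It is the approximate roll of the eligible intervention classes at two classes per grade, not a minimum number recruited. At the design's own entry requirement and the stated mean class size, 168 needs every family and child to agree. For consent between 70 and 95% the yield is about 118 to 160 intervention pupils, which is 50 to 8 fewer than stated.

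These numbers rest on assumed consent rates, which the protocol does not give and the pilot will help to establish. They show how sensitive the figure is; they do not predict a shortfall. They also assume 21 pupils per class and exactly two classes per grade; larger classes or schools would raise them.

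The consequence is moderate. The pilot is mainly descriptive and no analysis or decision in the protocol depends on 168. The correction is still worth making, because recruitment is among the things the pilot assesses and the stated benchmark equals full uptake.

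**What to change.** Rewrite the last sentence of section 3a so that it:

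1. gives 168 as the approximate number of pupils in eligible classes in the two intervention schools, with about 168 in the two control schools and 336 in total, at two classes per grade and 21 pupils per class;
2. drops the word minimum for recruited pupils;
3. gives the expected number of consented pupils per arm under a stated assumed consent rate (for illustration, 80% would give about 134 per arm and 269 in total);
4. separates pupils exposed through their class from pupils enrolled for measurement, and names the class headcount as the denominator of the consent rate.

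The cost is a small rewording and a stated expected sample below the present figure. No extra enrolment is needed, and no outcome or analysis changes.

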**Figure 2**

Overview of data collection process

[figure not shown]

**c.** Not applicable for the project

**4. Statistical considerations**

As this is a pilot study, the analysis will focus on the key parameters necessary for conducting a future trial. Most of the analysis will be descriptive in nature. Descriptive summaries will be generated to detect time and cost used, as well as recruitment process measures. Data on recruitment attrition and questionnaire response rates for pupils will be descriptively summarized and compared between the intervention school and the control school.

Interviews will be transcribed and uploaded into NVivo. Thematic analysis will be carried out for data analysis. This method allows identifying, analyzing, and reporting patterns within the data. Furthermore, it can be used as an essentialist method that reports experiences, meanings, and the reality of participants.

To investigate acceptability of the different intervention components, Qualitative Comparative Analysis (QCA) will be carried out. QCA is a case-oriented method to study complex phenomena originating from the comparative social sciences. This analysis can help identify differences in acceptability (i.e., demand and experiences) between the concerned parties and between the intervention components in order to investigate the mechanism(s). This will help optimizing the revised intervention for a large-scale effectiveness study. All researchers from the project group will validate the analysis, supported by the scientific and national advisory boards.

Preliminary effectiveness of the intervention on PL and well-being will be investigated using mixed models accounting the nested structure of the data. Descriptive statistics (e.g. means, SD) will provide some insight into population characteristics and give an indication of potential changes in mean scores between the two time points (i.e., pre-and postintervention).

**5. Participants**

**a.** Eligible classes for the study involve 4^th^ and 5^th^ graders, i.e., classes with pupils being 9-11 years of age.

A total of four public schools with a minimum of two classes per grade will be recruited and randomized to either the intervention or control condition.

The inclusion criteria are the following:

School/class-level

- Non-special needs municipal school classes
- Classes that are not in other school development or research projects which would most likely influence and bias the results

Pupil-level

- Pupils with parents/guardians who have provided written informed consent, allowing their child to participate

Pupils who have provide an oral assessment

**b.** None in addition to the inclusion criteria provide above.

**6. Risks, Side Effects and Disadvantages**

**a.** No biological measures will be collected. However, there may be risks of which we are not currently aware. Therefore, participants and their parents will be requested to inform any uncomfortable experiences or problems during their participation. In case of recurrent unforeseen ‘side effects’, the data collection procedures or any other parts of the pilot study will be discussed, and adaptions will be implemented to remove these side effects. In addition, the project “Danish Assessment of Physical Literacy” have documented that a small number of children, corresponding to approx. five out of 100, may experience skin irritation when having the Axivity® AX3 accelerometers mounted to the skin with skin tape. However, pupils and parents will be informed to de-mount the accelerometer if this should occur.

**b/c.** Not applicable for the project.

